## Abstract

Fabry disease (FD) is a rare genetic disorder caused by a deficiency in the α-galactosidase A enzyme, which results in the globotriaosylceramide accumulation in many organs, including the kidneys. Nephropathy is a major FD complication that can progress to end-stage renal disease if not treated early. Although enzyme replacement therapy and chaperone therapy are effective, other treatments such as ACE inhibitors and angiotensin receptor blockers can also provide nephroprotective effects when renal damage is also established. Recently, SGLT2 inhibitors have been approved as innovative drugs for treating chronic kidney disease. Thus, we plan a multicenter observational prospective cohort study to assess the effect of Dapagliflozin, a SGLT2 inhibitor, in FD patients with chronic kidney disease (CKD) stages 1–3. The objectives are to evaluate the effect of Dapagliflozin primarily on albuminuria and secondarily on kidney disease progression and clinical FD stability. Thirdly, any association between SGT2i and cardiac pathology, exercise capacity, kidney and inflammatory biomarkers, quality of life, and psychosocial factors will also be evaluated. The inclusion criteria are age ≥ 18; CKD stages 1–3; and albuminuria despite stable treatment with ERT/Migalastat and ACEi/ARB. The exclusion criteria are immunosuppressive therapy, type 1 diabetes, eGFR < 30 mL/min/1.73 m^2^, and recurrent UTIs. Baseline, 12-month, and 24-month visits will be scheduled to collect demographic, clinical, biochemical, and urinary data. Additionally, an exercise capacity and psychosocial assessment will be performed. The study could provide new insights into using SGLT2 inhibitors for treating kidney manifestations in Fabry disease.

## 1. Introduction

Fabry disease (FD) is a rare X-linked lysosomal storage disorder characterized by a deficiency in the activity of lysosomal α-galactosidase-A. This genetic mutation leads to the accumulation of globotriaosylceramide (Gb3) in various cell types, including endothelial, cardiac, renal, and neuronal cells, resulting in progressive damage to the renal, cardiac, and nervous system [1]. Kidney biopsies typically reveal Gb3 accumulation primarily in podocytes, mesangial cells, and tubular epithelial cells, with focal and global glomerulosclerosis usually starting in the second decade of life or even earlier in some cases [2,3]. It is worth noting that Gb3 accumulation alone is not solely responsible for the disease’s pathogenesis [4]. Inflammation and oxidative stress also contribute to organ damage, potentially explaining the suboptimal response of enzyme replacement therapy (ERT) in cases of late-disease diagnosis [5].

Clinically, three presentations of FD can be identified [1]. In hemizygous males with the classic form, the disease typically begins in childhood and presents with symptoms such as acroparesthesias, angiokeratomas, anhidrosis, cornea verticillate, and gastrointestinal disorders. Cardiac hypertrophy, arrhythmias, stroke, and chronic kidney disease usually appear later in life [6,7,8,9,10]. For heterozygous females, the clinical manifestations can vary widely, ranging from asymptomatic to mild or severe forms, and depend on the X-inactivation process. The FD later-onset form typically appears between the fourth and seventh decade of life and predominantly affects the heart or kidneys [11].

Nephropathy is a major FD complication, characterized by a reduced glomerular filtration rate and proteinuria. In the absence of a specific therapy, impaired renal function progressively worsens over time, leading to end-stage renal disease being reached around the fourth or fifth decade of life. Proteinuria is the primary predictor for renal progression in both men and women with FD [12]. Additionally, proteinuria is a risk factor for cardiovascular events in patients with chronic kidney disease (CKD) and, therefore, is an important therapeutic target.

The FD treatment involves specific therapy, such as enzyme replacement therapy using Agalsidase alpha/Agalsidase beta and chaperone therapy using Migalastat [13], which are aimed at managing organ damage [14,15]. However, there have been debates and conflicting results regarding the effect of these specific FD therapies on proteinuria in FD patients with CKD. Specifically, the use of Agalsidase alpha did not show any anti-proteinuric effect, while the reduction in proteinuria across clinical trials with Agalsidase beta varied significantly [16]. Furthermore, preliminary studies indicate conflicting results regarding the reduction in proteinuria with Migalastat [17].

In addition to the above therapies, other drugs such as ACE inhibitors (ACEi) and angiotensin receptor blockers (ARB) play a relevant nephroprotective role by reducing proteinuria and slowing the decline in the glomerular filtration rate (GFR). To achieve a nephroprotective effect, doses of ACEi/ARBs must be titrated to reduce proteinuria up to 0.5 g/24 h [18].

However, the use of ACEi or ARBs is limited due to the risk of hyperkalemia and acute kidney injury. Although a double blockade of ACEi and ARB demonstrated a greater antiproteinuric effect in patients with or without diabetes and with microalbuminuria or proteinuria, it is not recommended due to increased adverse events [19]. Furthermore, there is a lack of data available regarding the use of double blockade in Fabry nephropathy. 

SGLT2 inhibitors (SGLT2i), initially introduced as hypoglycaemic drugs, have become increasingly popular in recent years for the treatment of CKD and heart failure, regardless of glycaemic control. These drugs act by inhibiting the sodium–glucose cotransporters channels present in the S1 tract of the proximal tubule, which are responsible for the majority of filtered glucose reabsorption. Several large randomized controlled trials showed the benefits of SGLT2i in both cardiac and renal function, not only in patients with diabetes but also in patients without diabetes [20]. Indeed, SGLT2 inhibitors reduce the risk of cardiovascular death and hospitalization for heart failure similarly in patients with diabetes mellitus, hypertensive nephropathy, and glomerulonephritis. [21]. On the other hand, the results of two recent trials, such as EMPA-KIDNEY [22] and DELIVER [23], conducted in patients with or without diabetes mellitus have demonstrated that the use of SGLT2i reduced the risk of CKD progression (37%) and of acute kidney injury (AKI) onset (23%). These renal benefits were observed regardless of the underlying nephropathy or stage of glomerular filtrate rate [22]. An analysis of the DAPA-CKD trial [24] showed that dapagliflozin can significantly reduce albuminuria in CKD patients with and without diabetes mellitus. Consequently, SGLT2 inhibitors have been recently approved in CKD patients with proteinuria for the treatment of CKD progression [25].

SGLT2 inhibitors exert their nephroprotective effect through multiple mechanisms, including the re-establishment of glomerular tubular feedback, which protects against glomerular hyperfiltration damage. In depth, this involves the reduction in glucose and sodium reabsorption in the proximal tubule leading to increased sodium transport at the macula densa, increased adenosine release, afferent arteriole vasoconstriction, and a reduction in intraglomerular pressure [26]. These effects could be added to those of ACEi/ARBs, which act at the level of the efferent arteriole, causing vasodilation. 

In addition to these mechanisms, other factors can contribute to the nephroprotective effects of SGLT2 inhibitors, including the reduction in blood pressure values, an increase in hemoglobin and hematocrit values, a decrease in uric acid levels, and a reduction in oxidative stress and pro-inflammatory mediators [27,28]. 

These benefits suggest a potential role for SGLT2i in FD patients with CKD as these drugs could target the FD pathogenetic mechanisms, such as oxidative stress and inflammation, which are not completely addressed by ERT or chaperon therapy alone. However, further investigations and well-designed clinical trials are needed to thoroughly assess the effects of SGLT2i on Fabry nephropathy [29].

## 2. Aim of Study

With this background in mind, we have planned a multicenter observational prospective cohort study involving some Italian Nephrology and Internal Medicine Units. The study aims to evaluate the effect of an SGLT2 inhibitor, Dapaglifozin, in Fabry disease patients with CKD stages 1–3. Specifically, the primary objective will be to determine the effect of Dapaglifozin on albuminuria, with a target of achieving a 20% reduction in albuminuria. As secondary aim, we will assess the effect of Dapaglifozin on kidney disease progression, measured by a reduction in eGFR < 3 mL/min/1.73 m^2^ per year and on clinical FD stability, defined by a FAbry STabilization indEX (FASTEX) score < 20 [30]. Additionally, any association of SGT2i with the progression of cardiac pathology, exercise capacity, kidney and inflammatory biomarkers, quality of life, and psychosocial factors will be evaluated.

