## 3. Methods

The study was approved by the Hospital Ethics Committee for Clinical Trials CESC (Ref No. 5499/AO/22). The primary and secondary end-points will include albuminuria, estimated GFR calculated using the CKD-EPI formula, septum ventricular diameter and diastolic function detected at echocardiography, left ventricular mass index/m^2^ and evolution of T1 mapping pattern at magnetic resonance imaging (MRI), FASTEX score, 5 Times Sit to Stand Test (5STS) [31], 6 Minute Walking Test (6MWT) [32], Cardiopulmonary Exercise Testing (CPET), quality of life and psychosocial questionnaires, and urinary tract infections. In addition, the dosage of exomes, IgG, IgG4, kidney injury molecule-1 (KIM-1), neutrophil-gelatinase-associated lipocalin (NGAL), liver-fatty-acid-binding protein (LFABP), isoprostane, tumor necrosis factor alpha (TNF-alpha), interleukin-1 (IL-1), and interleukin-6 (IL-6) will be tested. 

The study will enroll male and female subjects aged 18 years or older with CKD stages 1–3, a genetic and biochemical diagnosis of FD and albuminuria for at least 6 months despite treatment with a stable dose of ERT or Migalastat for at least 12 months and ACEi or ARB titrated to the maximum tolerated dosage for at least 6 months. The subjects with immunosuppressive therapy, type 1 diabetes mellitus, eGFR < 30 mL/min/1.73 m^2^, and recurrent urinary tract infections will be excluded. 

On the basis of previous evidence [24], we estimated that at least 28 patients would need to be recruited to answer the research question with a 95% level of confidence and a margin of error of 5%.

The study will last two years and will include baseline, 12-month, and 24-month visits. 

At the baseline visit, the demographic data (age, sex), anamnestic data (comorbidities, medications, underling kidney disease), and clinical parameters (blood pressure, heart rate, height, weight, Body Mass Index [BMI]) will be collected. Biochemical examinations (LysoGb3, hematocrit, hemoglobin, fasting glucose, creatinine, urea, cystatin C, sodium, potassium, calcium, phosphorus, uric acid, total proteins, albumin, vitamin D, parathormone, brain natriuretic peptide [BNP], troponin I, polymerase chain reaction [PCR], exomes, IgG, IgG4, KIM-1, NGAL, LFABP, isoprostane, IL-1, TNF-alpha, IL-6, and homocysteine) and a urinary sample (creatinine, albumin, urea, sodium, potassium, phosphate, proteins, urine test, urine cultures) will also be tested.

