Additionally, the patient will undergo an exercise capacity assessment by means of the 6MWT, 5STS, and CPET tests and a psychosocial assessment using the following questionnaires: brief Illness Perception Questionnaire (BIPQ), Morisky Medication Adherence Scale 8 (MMAS-8), Chronic Illness Anticipated Stigma Scale (CIASS), Experience in Close Relationship Scale—Short Form (ECR-S), Health Care Relationship Trust Scale Revised (HCR-TS), Difficult Doctor–Patient Relationship Questionnaire 10 (DDPRQ-10), General Anxiety Disorder 7 (GAD 7), Patient Health Questionnaire 9 (PHQ-9), Edmonton Symptom Assessment System revised (ESAS-r), Severity of Dependence Scale (SDS), and Insomnia Severity Index (ISI). The qualities of life will be investigated using the 36-Item Short-form Survey (SF36). Finally, electrocardiogram (ECG), echocardiography, and cardiac MRI will be performed.

During the 12-month visit, the medical history will be updated, clinical parameters will be recorded, blood and urine tests will be repeated, the exercise capacity will be assessed using 6MWT, 5STS, and CPET, and the FASTEX Index will be also compiled.

At the 24-month visit, all the assessments and examinations from the baseline visit will be repeated. 

The statistical analysis will be performed using SPSS 21.0. The continuous variables will be presented as means and standard deviations, or medians and interquartile ranges depending on their distribution, which will be assessed using histograms and QQ plots. The nominal variables will be reported as frequencies and percentages. To determine any possible associations between SGLT2i and the variables of the primary and secondary outcomes, Pearson and Spearman tests will be used for continuous variables, the Fisher exact test for nominal variables, and the Student or Mann–Whitney tests for continuous and nominal variables. Finally, ANOVA tests will be performed for multicategory variables. A *p*-value of less than 0.05 will be considered statically significant for all tests. 

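### The primary 20% albuminuria target names neither a visit nor a unit (group change or per-patient threshold), and the listed tests do not estimate change from baseline

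*Protocol article*

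**What the plan says.** Section 2 (Aim of Study) gives the primary objective as the effect of the drug on albuminuria, "with a target of achieving a 20% reduction in albuminuria". The secondary aims in the same paragraph are also thresholds: a yearly eGFR loss below 3 mL/min/1.73 m² and a FASTEX score below 20.

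Section 3 (Methods) names the endpoint only inside a combined list: "The primary and secondary end-points will include albuminuria, estimated GFR calculated using the CKD-EPI formula", followed by many others. On timing it says "The study will last two years and will include baseline, 12-month, and 24-month visits". Albuminuria is available at all three visits:

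- Baseline: "a urinary sample (creatinine, albumin, urea, sodium, potassium, phosphate, proteins, urine test, urine cultures) will also be tested".
- Month 12: "blood and urine tests will be repeated".
- Month 24: "At the 24-month visit, all the assessments and examinations from the baseline visit will be repeated".

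The sample size, with the margin set at 5%, is justified as follows: "at least 28 patients would need to be recruited to answer the research question with a 95% level of confidence and a margin of error".

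The statistical paragraph of section 3 plans means or medians for continuous variables and frequencies for nominal ones. For associations with the drug it lists correlation tests, Fisher's exact test, Student or Mann-Whitney tests, and ANOVA. It adds that a "value of less than 0.05 will be considered statically significant for all tests". It does not mention the 20% target, a change from baseline or a responder proportion.

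**The concern.** A numerical target for a primary objective should be something a reader can check against the data. This one cannot be checked. Two post-baseline visits could carry it, and at each visit it could be a fall in a group summary or a fall in each patient. Those choices define the endpoint, and neither section 2 nor section 3 settles them. The listed tests do not help, because they relate drug exposure to outcomes and no unexposed group is described.

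The readings also behave very differently when the drug does nothing. A group mean over 28 patients averages out visit-to-visit variation in albuminuria. A per-patient threshold does not: some patients will be 20% lower at a later visit by variation alone. With no control group, nothing shows how large that share is. A responder percentage could therefore look like a drug effect when there is none, and more so if a fall at either visit counts.

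**Working it through.** **The plan's own figure.** The only design figure is 28 patients for 95% confidence and a 5% margin. The usual precision formula for a proportion, n = z²p(1−p)/e² with z = 1.96 and e = 0.05, gives 385 at p = 0.5 and 246 at p = 0.2. It gives 28 only if p is about 0.019, or with a finite-population correction for an unstated population of 29-30 (at p = 0.5). The 20% target does not enter. The origin of 28 is a separate question; here it is used only as the number of patients.

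**Inputs.**
- From the article: threshold 20%, so ln 0.80 = −0.223; n = 28; two post-baseline visits.
- Assumed, because the article gives no variability: within-patient CV of 15-50%, log-normal values, independent errors at the three visits, one measurement per visit, no true change and no time trend.

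**Formulas.**
- Within-patient SD on the log scale: σ = √ln(1 + CV²).
- SD of one patient's log change between two visits: s = σ√2.
- Chance of a fall of at least 20% in one patient: Φ(−0.223/s).
- Chance of a geometric-mean fall of at least 20% in 28 patients: Φ(−0.223√28/s).
- The either-visit rate was simulated, because the two changes share the baseline value.

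| CV | σ | s | One patient, one visit | Expected of 28 | Either visit | Group of 28, one visit |
|---|---|---|---|---|---|---|
| 15% | 0.149 | 0.211 | Φ(−1.06) = 15% | 4.1 | 23% | <0.01% |
| 20% | 0.198 | 0.280 | Φ(−0.80) = 21% | 6.0 | 33% | <0.01% |
| 30% | 0.294 | 0.415 | Φ(−0.54) = 30% | 8.3 | 44% | Φ(−2.84) = 0.2% |
| 50% | 0.472 | 0.668 | Φ(−0.33) = 37% | 10.3 | 53% | Φ(−1.77) = 3.9% |

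Requiring the fall at both visits gives 15% at CV 30% and 21% at CV 50%.

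**What averaging the two visits would gain.** With independent errors only, the variance of the change falls from 2σ² to 1.5σ², a cut of 25%. Power for a true 20% fall (paired t-test on the log scale, n = 28, two-sided 0.05) rises from 78% to 89% at CV 30% and from 40% to 50% at CV 50%. If the true log change also varies between patients with SD 0.3 (assumed), the variance at CV 30% goes from 2(0.294)² + 0.09 = 0.262 to 1.5(0.294)² + 0.09 = 0.219. That is a 16% cut, and power goes from 60% to 68%.

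**What a point-estimate condition would cost.** If the true ratio is exactly 0.80, the estimate falls at or below 0.80 half the time. Requiring that as well as an upper limit below 1 is therefore met at most 50% of the time. Simulation for one visit gives 50% at CV 30% and 39% at CV 50%; in the latter case the confidence limit binds more often.

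**The case against.** The strongest reply is that this is a condensed article. Visit and summary measure may be fixed in a fuller protocol or analysis plan that is not shown, and nothing quoted contradicts anything else. That limits what can be said about intent. It does not remove the point, because the article itself states a numerical primary target, and states it in a form that cannot be evaluated.

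The second reply is that the text never adopts a per-patient rule. It speaks of a target, lists albuminuria itself as the endpoint, and plans means or medians for continuous variables. This is right. A reader might infer that success will be a responder count, and that about a third of patients will succeed by chance. The documents support neither step. The per-patient reading remains possible because the secondary aims are thresholds and the sample-size sentence has the form used for a proportion, but it is only one reading. The chance rate depends on an assumed CV and falls to 15-21% at CV 15-20%. Nor do the documents show that a 20% fall is smaller than ordinary within-patient variation.

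A reader might also infer that the reading will be picked after the data are seen. No passage says so; the article merely does not prevent it. A single urine sample per visit is likewise inferred from the wording, and averaging several would lower the chance rate.

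**Conclusion.** The point holds in a limited form. Without any assumption, the primary target has no visit, no stated unit or summary measure, and no listed test that estimates it. Conditional on a per-patient reading with no control group, roughly 15-37% of patients would meet it at one visit with no drug effect (30-37% at CV 30-50%), and 23-53% if either visit counts. A group geometric-mean fall of 20% would occur by chance in under 4% of studies. All these rates rest on the assumed CV, log-normal values, independent errors and no time trend, and serve as illustration only. The gap should be closed, since it concerns the study's primary conclusion, but it does not show that the study plans a misleading analysis.

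**What to change.** Define the primary endpoint as the geometric mean ratio to baseline of urine albumin-to-creatinine ratio at one named visit, with its 95% CI from the within-patient log changes. Conclude a reduction if the upper limit is below 1, and report the estimate against 0.80. Keep the share of patients with a 20% fall as a descriptive figure. If claiming the 20% target also requires an estimate at or below 0.80, say that this would be met at most about half the time when the true fall is exactly 20%.

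Averaging months 12 and 24 is an optional alternative. It cuts the variance by at most 25%, less if response varies between patients. The result is not a pure 24-month effect, so month 24 should then be shown alongside.

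The cost is a few sentences. Urine albumin and creatinine are already in the test list, and no visit is added. The change does not supply a comparator, so a fall from baseline would still not separate drug effect from other changes over time.

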## 3. Methods

The study was approved by the Hospital Ethics Committee for Clinical Trials CESC (Ref No. 5499/AO/22). The primary and secondary end-points will include albuminuria, estimated GFR calculated using the CKD-EPI formula, septum ventricular diameter and diastolic function detected at echocardiography, left ventricular mass index/m^2^ and evolution of T1 mapping pattern at magnetic resonance imaging (MRI), FASTEX score, 5 Times Sit to Stand Test (5STS) [31], 6 Minute Walking Test (6MWT) [32], Cardiopulmonary Exercise Testing (CPET), quality of life and psychosocial questionnaires, and urinary tract infections. In addition, the dosage of exomes, IgG, IgG4, kidney injury molecule-1 (KIM-1), neutrophil-gelatinase-associated lipocalin (NGAL), liver-fatty-acid-binding protein (LFABP), isoprostane, tumor necrosis factor alpha (TNF-alpha), interleukin-1 (IL-1), and interleukin-6 (IL-6) will be tested. 

The study will enroll male and female subjects aged 18 years or older with CKD stages 1–3, a genetic and biochemical diagnosis of FD and albuminuria for at least 6 months despite treatment with a stable dose of ERT or Migalastat for at least 12 months and ACEi or ARB titrated to the maximum tolerated dosage for at least 6 months. The subjects with immunosuppressive therapy, type 1 diabetes mellitus, eGFR < 30 mL/min/1.73 m^2^, and recurrent urinary tract infections will be excluded. 

On the basis of previous evidence [24], we estimated that at least 28 patients would need to be recruited to answer the research question with a 95% level of confidence and a margin of error of 5%.

The study will last two years and will include baseline, 12-month, and 24-month visits. 

At the baseline visit, the demographic data (age, sex), anamnestic data (comorbidities, medications, underling kidney disease), and clinical parameters (blood pressure, heart rate, height, weight, Body Mass Index [BMI]) will be collected. Biochemical examinations (LysoGb3, hematocrit, hemoglobin, fasting glucose, creatinine, urea, cystatin C, sodium, potassium, calcium, phosphorus, uric acid, total proteins, albumin, vitamin D, parathormone, brain natriuretic peptide [BNP], troponin I, polymerase chain reaction [PCR], exomes, IgG, IgG4, KIM-1, NGAL, LFABP, isoprostane, IL-1, TNF-alpha, IL-6, and homocysteine) and a urinary sample (creatinine, albumin, urea, sodium, potassium, phosphate, proteins, urine test, urine cultures) will also be tested.

Additionally, the patient will undergo an exercise capacity assessment by means of the 6MWT, 5STS, and CPET tests and a psychosocial assessment using the following questionnaires: brief Illness Perception Questionnaire (BIPQ), Morisky Medication Adherence Scale 8 (MMAS-8), Chronic Illness Anticipated Stigma Scale (CIASS), Experience in Close Relationship Scale—Short Form (ECR-S), Health Care Relationship Trust Scale Revised (HCR-TS), Difficult Doctor–Patient Relationship Questionnaire 10 (DDPRQ-10), General Anxiety Disorder 7 (GAD 7), Patient Health Questionnaire 9 (PHQ-9), Edmonton Symptom Assessment System revised (ESAS-r), Severity of Dependence Scale (SDS), and Insomnia Severity Index (ISI). The qualities of life will be investigated using the 36-Item Short-form Survey (SF36). Finally, electrocardiogram (ECG), echocardiography, and cardiac MRI will be performed.

During the 12-month visit, the medical history will be updated, clinical parameters will be recorded, blood and urine tests will be repeated, the exercise capacity will be assessed using 6MWT, 5STS, and CPET, and the FASTEX Index will be also compiled.

At the 24-month visit, all the assessments and examinations from the baseline visit will be repeated. 

The statistical analysis will be performed using SPSS 21.0. The continuous variables will be presented as means and standard deviations, or medians and interquartile ranges depending on their distribution, which will be assessed using histograms and QQ plots. The nominal variables will be reported as frequencies and percentages. To determine any possible associations between SGLT2i and the variables of the primary and secondary outcomes, Pearson and Spearman tests will be used for continuous variables, the Fisher exact test for nominal variables, and the Student or Mann–Whitney tests for continuous and nominal variables. Finally, ANOVA tests will be performed for multicategory variables. A *p*-value of less than 0.05 will be considered statically significant for all tests. 

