## 4. Conclusions

This study will be the first in the literature to evaluate the effect of Dapaglifozin in patients with albuminuria affected by CKD secondary to Fabry’s disease, primarily on renal outcomes (albuminuria and CKD progression) and, secondarily, on cardiovascular outcomes, exercise capacity, and quality of life. It will provide new compelling evidence on the use of SGLT2 inhibitors in the field of rare diseases.

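### An uncontrolled cohort with one listed baseline urine sample is said to determine the effect of dapagliflozin on albuminuria; earlier stable-period values could sharpen the baseline, and the conclusion should be worded as a within-patient association

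*Protocol article*

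**What the plan says.** The Aim of Study section describes the design: "we have planned a multicenter observational prospective cohort study involving some Italian Nephrology and Internal Medicine Units". No untreated, concurrent or historical group appears there or in Methods. The aim is worded causally: "the primary objective will be to determine the effect of Dapaglifozin on albuminuria", "with a target of achieving a 20% reduction in albuminuria". The section does not say whether the 20% applies to the group or to each patient, against which value it is measured, or at which visit.

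Methods gives the schedule: "The study will last two years and will include baseline, 12-month, and 24-month visits". For albuminuria at baseline it says that "a urinary sample (creatinine, albumin, urea, sodium, potassium, phosphate, proteins, urine test, urine cultures) will also be tested". Entry requires "albuminuria for at least 6 months despite treatment with a stable dose of ERT or Migalastat for at least 12 months", together with "ACEi or ARB titrated to the maximum tolerated dosage for at least 6 months". Methods itemises the data to be collected, and pre-enrolment albuminuria is not among them. The analysis paragraph names tests of association between SGLT2 inhibition and the outcomes. It does not mention the stable period before treatment.

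The Conclusions section states: "It will provide new compelling evidence on the use of SGLT2 inhibitors in the field of rare diseases".

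**The concern.** Without a comparator, the only contrast the article offers for its primary aim is later albuminuria against baseline. That contrast contains the drug effect plus three other things: any trend already under way on Fabry therapy and ACEi/ARB, any change in other care over two years, and regression to the mean if a high baseline value was what let the patient in. With one listed sample, the baseline is also noisy.

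Two things are at stake. The first is the claim: taken as described, the study would announce an effect that its design cannot isolate. The second is precision: the entry rule implies that earlier results on stable treatment are in the records, and leaving them out gives up information in a study of 28 patients.

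**Working it through.** **Inputs.** From the article: target ratio 0.80, so d = −ln 0.8 = 0.223; n = 28; alpha 0.05, taken as two-sided; visits at 0, 12 and 24 months. The article gives no variance, drift rate or albuminuria cut-off, so those below are assumptions. It also gives no figure on this point to reproduce. The 28 is taken as given; how it was obtained is a separate question.

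**1. Regression to the mean, no drug effect.** Simulated log-normal albuminuria, entry cut 30 mg/g, median 60 to 150 mg/g, between-patient log SD 1.0 to 1.2, within-patient log SD s 0.35 to 0.45.

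| Entry rule | Apparent change in group mean |
|---|---|
| Baseline sample qualifies the patient | −1.5% to −7.8% |
| An earlier sample and the baseline sample must both qualify | −1.0% to −5.1% |
| Only an earlier sample qualifies; baseline is separate | about 0% |

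With wider inputs (median 60 to 200, between-patient SD 0.8 to 1.2, s 0.3 to 0.5) the first row runs from −0.4% to −9.9%. No scenario reaches −20%.

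**2. Drift.** A trend of −10% per year gives 0.9² = 0.81 at 24 months, a 19% fall with no drug effect. A trend of +10% per year gives 1.1² = 1.21, which would hide a real fall. The article gives no rate or direction for treated patients.

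**3. Effect of a spurious shift on the test.** With SE = s√(2/28), a 10% shift from any source gives P(significant fall) = Φ(−ln 0.9/SE − 1.96):
- s = 0.3: SE 0.080, probability 26%.
- s = 0.5: SE 0.134, probability 12%.

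The nominal rate in that direction is 2.5%.

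**4. Per-patient reading of the target.** With no drug effect and one sample at each time, P(fall of 20% or more) = Φ(−0.223/(s√2)), where s = √ln(1 + CV²). This gives 29.5%, 34.1% and 36.9% at CV 30%, 40% and 50%, or about 8 to 10 of 28 patients. Noise with mean zero does not move the group mean, so these figures apply to a responder count only.

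**5. Gain from averaging the baseline.** SD of change = s√(1 + 1/k) with k baseline values; power from a two-sided paired t test, n = 28, 20% fall.

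| Assumption | k = 1 | k = 3 |
|---|---|---|
| s = 0.45 | SD 0.636, power 43% | SD 0.520, power 59% |
| CV 30% (s = 0.294) | SD 0.415, power 78% | SD 0.339, power 92% |
| s = 0.45, response SD 0.5 between patients | SD √(0.636² + 0.5²) = 0.809, power 29% | SD √(0.520² + 0.5²) = 0.721, power 35% |

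**6. Projecting each patient's own slope instead.** The variance of the projected value is s²[1/k + (T − t̄)²/Σ(t − t̄)²]. Take s = 0.45 and equally spaced values ending at baseline.
- Three values over 6 months: at T = 1 year the bracket is 1/3 + 1.25²/0.125 = 12.83, so the SD of change is 0.45√13.83 = 1.67 and power is 10%. At 2 years power is 7%.
- Five values over 12 months: power is 21% at 1 year and 12% at 2 years.

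All four are far below the 43% from a single baseline value.

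**The case against.** The strongest reply has five parts.

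- **Change from baseline is not written out.** True. It is inferred from the 20% target and the visits. The inference is reasonable because the article describes no other contrast for its primary aim, but it remains an inference.
- **A condensed article may omit the baseline definition and the use of past records.** This stands in part. Silence about abstraction is not an error in itself, and naming one urine sample does not exclude repeat collection. What the article does state is a causal aim and a strong conclusion, from a design with no described comparator.
- **Six months of persistent albuminuria already guards against regression to the mean.** Largely right. A reader might infer that regression could produce the whole 20% target. The documents do not support that: they do not say that the baseline sample decides entry, and the simulated size is about 1 to 8% if it does and about 0% if it does not.
- **The 30 to 37% noise figure shows that apparent success is likely by chance.** Only if the target is read patient by patient, which the article leaves open.
- **The pre-treatment period could serve as a full self-control, slope included.** This is tempting but fails in the main analysis. Slope projection cuts power to about 7 to 21%. Values from months 7 to 12 before entry may also predate full ACEi/ARB titration, because that therapy is guaranteed for 6 months only. Such values could raise the pre-treatment level and exaggerate the fall.

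**Conclusion.** The point holds in limited form. As described, a fall in albuminuria could not be attributed to dapagliflozin, so the effect wording and the promise of compelling evidence go beyond the design. Drift and other changes in care are the main unresolved alternatives. Drift may go either way, so it could hide a benefit as well as imitate one. Regression to the mean is a modest addition that depends on an entry rule the article does not spell out.

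A reader might go further and conclude that a positive result would carry no information. That does not follow: a clear group fall after a documented stable period would be a useful within-patient association in a rare disease, short of a controlled effect.

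The recoverable loss of precision is real but conditional: 43% to 59% power at s = 0.45, 78% to 92% at CV 30%, and 29% to 35% if response varies with SD 0.5. It assumes three usable baseline values per patient. All variances, the 30 mg/g cut and the drift rates are assumptions. The matter should be addressed, but it does not make the study unworkable.

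**What to change.** 1. **Baseline.** Abstract existing albumin/creatinine results from the period when both Fabry therapy and maximum tolerated ACEi/ARB were already stable, which is at least the last 6 months. Define baseline log albuminuria as the mean of the baseline-visit sample and those values, excluding every value used to establish eligibility. Showing six months of albuminuria takes at least two results, so state what is done when few or none remain.
2. **Main comparison.** Compare the on-treatment level with this pre-treatment level as a group geometric mean ratio with 95% confidence interval, and state that the 20% target refers to that ratio. Report per-patient responders descriptively. Show the pre-treatment trend as a sensitivity analysis only.
3. **Wording.** State the aim and conclusion as a within-patient association that needs controlled confirmation. Averaging the baseline does not remove drift or changes in care after the start, so this step is needed even if the first two are taken.

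The cost is chart abstraction and rewording, with no extra patients or visits. The downsides are variable numbers of historical values, possibly from different laboratories, and a more modest claim.
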